#### Procedures

Eligible participants are invited to complete questionnaires on Qualtrics software (49) and receive automatic prompts to ensure all items are responded to, and those who do not complete questionnaires within 1 week are reminded. Once randomised, participants receive interventions as outlined below. A final telephone call (5–10 min) by a research assistant blinded to group allocation is made to all participants. In this telephone call, the DSISD Insomnia module is administered to determine the presence/absence of insomnia disorder and assess risk. All telephone communications are audio-recorded for assessing reliability and intervention fidelity.

### Interventions

All participants, regardless of group allocation, continue usual postpartum care. No participants are restrained from seeking treatment or support for sleep concerns. Treatment or support received outside of the study interventions are documented.

Interventions include therapist-assisted and self-directed/automated components which are delivered via distance. Interventions are manualised and telephone scripts were developed by the research team to ensure consistency. A provisional psychologist undertaking doctoral training in clinical psychology (SV) who was trained prior to trial commencement in CBT for insomnia delivery by a clinical psychologist (BB) carries out intervention telephone calls and receives regular supervision throughout the trial.

#### Cognitive Behavioural Therapy

The CBT material is based on CBT for insomnia adapted for perinatal populations (22, 50). This mode of treatment has been identified as the intervention of choice by pregnant women and their partners compared to pharmacotherapy and no treatment (51). To adapt intervention for later postpartum months, a focus group with four new mothers was carried out to aid intervention development and provided guidance on content and delivery format. Strategies are delivered via emails which are designed to be visually-attractive, easy-to-read and brief (see Supplementary Material), in light of recommendations provided in the focus group. Components of the CBT intervention include: psychoeducation, stimulus control, healthy attitudes and behaviours around sleep, sleep hygiene, relaxation, managing unhelpful thoughts and worries, fatigue management, prioritising rest and self-care, enlisting social support and infant settling. Emails are delivered using an online software that provides professional email templates and automates the timing of intervention delivery based on each woman's own progress. In total, 21 emails are delivered: five in Week 1, four in Week 2, followed by three emails per week in Weeks 3 to Week 6.

#### Light Dark Therapy

Participants in the LDT group are provided with light therapy glasses (Luminette 2) and are asked to wear them for at least 20 (but no more than 30) min each morning immediately upon waking. The light glasses are fixed at the brightest factory setting and provide white light [Correlated Colour Temperature (CCT) = 5,260 Kelvin] which is blue-enriched with a peak spectral wavelength of 466 nm at an intensity of 1,250 lux directed at each eye measured via spectrophotometry. The melanopic lux of the light glasses was 813 lux, calculated using the International Commission on Illumination system [CIE; (52)]. Light glasses have received the EC Full Quality Assurance Certificate from SGS, Belgium (Directive - 93/42/EEC). Participants receive a Luminette User Manual for further detailed information regarding their light glasses. Participants are also provided light hygiene strategies regarding strategies regarding light exposure during both day and night. These include seeking natural bright light to promote alertness during the day and light avoidance in the hours prior to nighttime sleep, especially blue light from hand-held electronic devices. A small LED night light (Dreambaby Auto Sensor Swivel Light) is provided to participants to use during nighttime awakenings (e.g., overnight infant care). The night light has been tested using spectrophotometry and yields 5 lux at 12 inches distance (CCT = 5,754 Kelvin) and 4 melanopic lux (52). Brief weekly emails are sent from Week 1 to Week 6 to remind participants of pertinent strategies and encourage intervention adherence. After completing final assessments at T4, LDT participants receive the CBT intervention emails in bulk.

#### TAU Control

Participants in the TAU condition complete assessments at all time points and continue to receive usual postnatal care. After completing final assessments at T4, TAU participants receive CBT intervention emails.

#### Therapist Assistance

Participants in CBT and LDT conditions receive two scheduled telephone calls with a provisional psychologist: (1) an orientation telephone call in Week 1 which aims to: (a) explain key components of the interventions, (b) provide personalised recommendations, and (c) encourage intervention adherence, and (2) a mid-point telephone call. Participants in intervention conditions all receive core components of interventions as listed above however components specifically relevant to the individual are highlighted. For example, relaxation strategies may be highlighted for a participant who reports feelings of tension around sleep onset or addressing dysfunctional beliefs about sleep for another participant who presents with high sleep-related anxiety. LDT is personalised by providing a specific time to begin light glasses usage based on habitual wake time and selecting an optimal location for the night light in the home.

Orientation telephone calls takes ~45 min for those in the LDT condition and 60 min for those in the CBT condition. Following the orientation telephone call, LDT participants are provided with a two-page summary of key points, including reminder of personalised time to commence light glasses usage in the morning. During the orientation telephone call, TAU participants are thanked for their involvement and reminded of project logistics (~10 min).

##### Mid-point Telephone Call

All participants receive a telephone call in Week 3 (for CBT and LDT group, this is intervention mid-point). The purpose of the telephone call for those in intervention conditions is to ascertain and encourage intervention adherence, and problem-solve any obstacles to utilising intervention strategies. Participants in intervention conditions are encouraged to keep using intervention strategies beyond the sixth week. Those in the TAU condition are thanked for their ongoing participation and discuss any questions related to logistic aspects of participation. As previously mentioned, a risk assessment is undertaken in the mid-point telephone call.

### Adverse Events

Risk is minimised by early exclusion of women for whom participation may pose a risk of harm (e.g., those with photosensitivity, severe psychopathology, epilepsy etc.). Any risk issues are documented in a tracking sheet, including any internal consultations and actions decided (e.g., referral following exclusion) by the research team. During screening, a physician with extensive experience in sleep medicine is consulted when clarification of inclusion/exclusion criteria is required (e.g., use of medication, medical conditions).

Side-effects of participation are assessed in the two final questionnaires. Participants are asked to report any side-effects of LDT immediately so that intervention may be appropriately adapted (e.g., ensuring sufficient ambient light exposure during glasses usage, delaying use of glasses, substitution of glasses usage with natural light exposure). Women who report side-effects are monitored via telephone and email to ensure adherence with recommendations to minimise harm. A physician is consulted in the event of adverse events. Any adverse events that occur throughout the trial are recorded in a tracking sheet.

Any protocol modifications are first approved by Monash University Human Research Ethics Committee before being implemented and communicated to participants if relevant. Long-lasting, serious harm is not expected as a result of trial participation which is explicated in the explanatory statement.

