## Abstract

**Background:** Symptoms of insomnia are common in new mothers and have been associated with a range of negative maternal and child outcomes. Despite this, interventions to improve maternal postpartum sleep remain scarce. Cognitive Behavioural Therapy (CBT) and Light Dark Therapy (LDT) represent two promising interventions for insomnia symptoms and associated daytime consequences such as fatigue. This randomised controlled trial examines whether CBT and LDT improve maternal insomnia symptoms as the primary outcome and maternal sleep disturbance, mood, fatigue, and sleepiness as secondary outcomes. This protocol paper outlines the development, design, and implementation of the trial.

**Methods:** Participants are an Australian community-sample of 90 first-time mothers who are 4–12 months postpartum with self-reported symptoms of insomnia (Insomnia Severity Index scores ≥ 8). Exclusion criteria include current severe sleep/psychiatric disorders, unsettled infant sleep behaviour, sleep-affecting medication use, and photosensitivity. Eligible women are randomised into a CBT (strategies targeting sleep, worries, fatigue, and relaxation), LDT, or a treatment-as-usual control condition. Interventions are therapist-assisted and personalised through two telephone calls and include a series of automated intervention emails delivered over 6 weeks. Primary and secondary outcomes are assessed at four time points: baseline, intervention mid-point, post-intervention, and 1-month post-intervention.

**Discussion:** If found effective, these interventions could represent efficacious, safe, and inexpensive treatments for improving postpartum insomnia and mitigate its negative impact on maternal well-being. Interventions tested are highly scalable and can be integrated into postpartum care and made available to the broader community.

**ANZCTR trial registration:** Accessible at: https://anzctr.org.au/Trial/Registration/TrialReview.aspx?ACTRN=12618000842268.

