## Data Analysis

### Sample Size and Power

Assuming 5% missing data at T0, 10% missing data at T2, and 15% missing data at T3 (53), a sample size of 90 powered adequately at 82% (two tailed α = 0.05) to detect a medium effect size (*f* = 0.25), which was observed in a recent CBT for insomnia trial on prenatal insomnia (22).

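### Before Week 6, side-effects are collected only passively, and the only stated request to report them names LDT, so pooled counts may not be comparable across arms

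*Protocol article*

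**What the plan says.** Under Adverse Events, the protocol article sets the timing of solicited enquiry: "Side-effects of participation are assessed in the two final questionnaires". Table 1 shows that these are T3 (Week 6) and T4 (Week 10). A T2 questionnaire goes to all three arms at Week 3, but side-effect items are not said to be part of it.

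The same section adds one route for earlier reports: "Participants are asked to report any side-effects of LDT immediately so that intervention may be appropriately adapted". No matching request is described for CBT or TAU. Women who report side-effects are then followed by telephone and email.

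A general record is also kept: "Any adverse events that occur throughout the trial are recorded in a tracking sheet". It is not limited to one arm, but the article does not say how events are elicited.

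Under Mid-point Telephone Call, "All participants receive a telephone call in Week 3". In the intervention arms its purpose is "to ascertain and encourage intervention adherence, and problem-solve any obstacles to utilising intervention strategies". In the control arm, "Those in the TAU condition are thanked for their ongoing participation and discuss any questions related to logistic aspects of participation". The call includes a risk assessment, which the Risk Assessment section confines to suicidal or homicidal risk, injurious behaviour and contact with mental health care.

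The Abstract says that, if the trial finds an effect, "these interventions could represent efficacious, safe, and inexpensive treatments for improving postpartum insomnia".

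**The concern.** The intervention runs for six weeks, and the first structured side-effect question comes at its end. A woman who has a problem in the first weeks and leaves the study before T3 has no stated structured opportunity to report it. A woman who stays must recall at Week 6 what happened in Week 1.

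The early routes are also uneven. LDT participants are asked to report at once, and a report brings further contact and so further chances to record an event. For CBT no such request is described. If early reports and questionnaire answers are pooled into one count per arm, LDT could look worse than CBT with no true difference in tolerability.

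At stake is how far the trial's own harms data can support the word safe in the Abstract. The Discussion says that, to the authors' knowledge, no trial of this kind has been done beyond the fourth postpartum month, so those data will matter to readers.

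**Working it through.** The article gives no expected side-effect rate and no safety comparison, so there is no figure of its own to reproduce. The check sets the early contacts side by side and then brackets the size.

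**Step 1. What is asked before T3, by arm (Adverse Events; Mid-point Telephone Call; Risk Assessment; Table 1)**

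| Contact before Week 6 | CBT | LDT | TAU |
|---|---|---|---|
| Solicited side-effect items | none stated | none stated | none stated |
| Request to report side-effects at once | none stated | yes | none stated |
| Week 3 call: adherence and obstacles | yes | yes | no (logistics) |
| Week 3 call: risk assessment | yes | yes | yes |
| Tracking sheet for adverse events | yes | yes | yes |

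The only row that names side-effects and has an entry applies to LDT alone.

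**Step 2. How many women miss the first solicited question**

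Inputs: 90 women (Sample Size and Power); 1:1:1 allocation (Design), so about 30 per arm; 10% missing at T2 and "15% missing data at T3" (Sample Size and Power).

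- Missing at T3: 90 × 0.15 = 13.5 in total, or 30 × 0.15 = 4.5 per arm.
- Missing at T2: 30 × 0.10 = 3 per arm.

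The 4.5 is the number expected to miss T3, not the number never asked. T4 asks again, and no missing rate is given for T4.

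If dropout is monotone (an assumption), 4.5 − 3 = 1.5 women per arm would answer at T2 but not at T3. T2 items alone would therefore recover only about a third of those missing at T3, which is why a question at withdrawal is also needed.

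**Step 3. How far the solicited rate could be understated (assumed values only)**

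Let p be the true rate, 15% the overall dropout before being asked, and k the ratio of dropout in women with side-effects to dropout in women without.

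- Dropout without side-effects: b = 0.15 / (1 − p + pk).
- Rate among those asked: p(1 − kb) / 0.85.

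For p = 10% and k = 2: b = 0.15/1.1 = 0.136, kb = 0.273, and the rate is 0.10 × 0.727/0.85 = 8.6%.

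| True rate | k = 1 | k = 2 | k = 3 |
|---|---|---|---|
| 10% | 10.0% | 8.6% | 7.4% |
| 20% | 20.0% | 17.6% | 16.0% |

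The article gives neither p nor k. At k = 1 there is no understatement.

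**Step 4. What the sample size allows in any case**

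With no events among n women, the exact one-sided 95% upper bound is 1 − 0.05^(1/n). This is 9.5% for n = 30 and 11.3% for n = 25. Even complete, even-handed ascertainment with no side-effects would leave a rate of nearly one in ten in an arm unexcluded.

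**The case against.** The strongest reply is that there is no planned safety analysis to bias. The aims and hypotheses concern efficacy, the Statistical Analysis section describes no between-arm comparison of side-effects, and the Abstract's wording is conditional. The T3 and T4 items are not stated to differ by arm, so a comparison limited to them would be even-handed among responders. This stands. A reader might infer that the trial plans to conclude that the interventions are safe and that its data cannot support this. The article supports neither part, and the point is only that the word needs qualifying.

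Second, early dropouts are not without contact. Every arm gets the Week 3 call, CBT and LDT women alike are asked about obstacles, adverse events are recorded in all arms, and fatigue, sleepiness, mood and insomnia scales are completed at T2. This stands in part: a CBT problem could surface on the call. None of these contacts is a stated side-effect enquiry, however, and the symptom scales cannot separate a side-effect from the symptoms being treated.

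Third, the LDT request serves to adapt the intervention and is not presented as a way of comparing harms. That is fair, and nothing here argues against having it. Its by-product is still an extra reporting route in one arm.

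Fourth, the article condenses a fuller protocol that may say how adverse events are elicited. This limits the point to what the article does fix, namely the T3 and T4 timing and the LDT-specific request.

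**Conclusion.** The point holds as a modest design weakness with a cheap remedy. As described, side-effect ascertainment before Week 6 is passive, and the request to report names one intervention arm. Two consequences follow. Pooled counts may be higher in LDT from ascertainment alone, and women who leave before T3 may go unasked.

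The size is uncertain. About 4.5 of 30 women per arm are expected to miss T3, fewer if some answer at T4. Under the assumed rates and dropout ratios shown, the solicited rate would lie between its true value and about a quarter below it (10% read as 7.4%).

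A reader might infer that solicited rates are certain to be too low, or that a definite percentage of side-effects will be missed. The article supports neither reading, because it gives no side-effect rate and no link between side-effects and dropout. Nor does it show that a comparison of arms is certain to be biased, since none is planned. The conclusion assumes about 30 women per arm and that the full protocol adds no structured side-effect enquiry before T3.

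**What to change.** 1. Add the side-effect items already used at T3 and T4, identically worded, to the T2 questionnaire in all three arms.
2. Ask the same items once at withdrawal, because T2 alone misses women who leave before Week 3.
3. Make the request to report problems between visits the same for CBT and LDT.
4. Base any between-arm statement about side-effects on solicited answers only, and list spontaneous reports separately by arm.
5. Qualify the word safe in the Abstract and in later reports, giving the number of women asked and an upper confidence limit for the rate in each arm.

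The first three steps cost a few online items, a short question at withdrawal and an ethics amendment, with a small added burden on participants. Recruitment began in October 2018, so women already past Week 3 will have no T2 reading. Reports should therefore state how many women were asked at each time point under each version of the questionnaire. Steps 4 and 5 need no new data and also apply to women already enrolled.

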### Measurements

Questionnaires include various self-report measures of sleep, mental health, fatigue, perceived stress, social support, self-efficacy, and relationship satisfaction among other factors. Self-report sleep measures with strong psychometric properties were selected for primary and secondary outcomes as self-reported sleep complaints (not objectively-assessed sleep parameters) share strong associations with other well-being outcomes (53). Further, insomnia, the primary outcome of this trial, is assessed and diagnosed based on self-reported sleep complaints (54). To reduce study burden for this vulnerable population, we did not include objective measures of sleep. Please see Table 1 for a list of measures and their associated timing.

**Table 1 T1:** Timing of measurements.

	**Enrolment**	**Allocation**	**Post-allocation**			
**Timepoint**	**T0**	**0**	**T1**	**T2**	**T3**	**T4**
**Enrolment**						
Consent and Screen	X					
Randomisation		X				
**Intervention**						
CBT						
LDT						
TAU						
**Structured interviews**						
Duke structured interview for sleep disorders	X				^*^	
**Primary outcome**						
Insomnia severity index	X			X	X	X
**Secondary outcomes**						
PROMIS sleep disturbance – SF	X			X	X	X
Fatigue assessment scale (5-item, modified)	X			X	X	X
Visual analog scale of fatigue	X			X	X	X
PROMIS anxiety – SF	X			X	X	X
PROMIS depression – SF	X			X	X	X
Epworth sleepiness scale	X			X	X	X
Karolinska sleepiness scale	X			X	X	X
**Other factors**						
Demographic and obstetric information	X				^∧^	^∧^
Postnatal questions on sleep timing, duration and quality	X			X	X	X
Dysfunctional beliefs about sleep scale	X			X	X	X
Morningness-eveningness questionnaire	X			X	X	X
Glasgow sleep effort scale	X			X	X	X
Brief infant sleep questionnaire	X			X	X	X
Perceived stress scale	X			X	X	X
PROMIS emotional support – SF	X			X	X	X
PROMIS instrumental support – SF	X			X	X	X
Maternal efficacy questionnaire	X				X	X
Mother to infant bonding scale	X				X	X
Dyadic adjustment scale – 4	X				X	X
Cross-cutting symptoms level 1	X				X	
Ford insomnia response to stress test	X					
Maternal sleep history questions	X					
Credibility expectancy questionnaire	X					
Intervention adherence and usefulness^#^					X	^∧^
Client satisfaction questionnaire^#^					X	
COVID-19 questions						X

*T0, Pre-study screening/consent and baseline; T1, Time-point 1 (Week 0) intervention start; T2, time-point 2 (Week 3) intervention mid-point; T3, time-point 3 (Week 6) immediate post-intervention; T4, time-point 4 (Week 10) 1-month follow-up; CBT, Cognitive Behavioural Therapy; LDT, Light Dark Therapy; TAU, treatment-as-usual; X, Measure administered at that time point*;

* *Insomnia module administered only (10 mins)*;

∧ *only a subset of questions asked*;

# *not administered to TAU; SF, short form*.

#### Primary Outcome

The ISI is a 7-item measure of self-reported insomnia symptoms (44) and is used as the primary outcome. Total scores range from 0 to 28, with higher scores indicating more severe insomnia symptoms. Items such as “*difficulty falling asleep*” and “*difficulty staying asleep*” are rated on a 5-point Likert-type severity scale (“*during the past 2 weeks*”), ranging from 0 = none to 4 = very severe. Scores of 0-7 = no clinical insomnia symptoms; 8–14 = sub-threshold insomnia; 15–21 = moderate clinical insomnia; and 22–28 = severe clinical insomnia (55). The ISI has been shown to have high internal consistency and a cutoff score of ≥8 has a sensitivity 96–99% and specificity of 78–92% in community and clinical populations respectively (56).

#### Secondary Outcomes

Maternal sleep quality, measured using PROMIS Sleep Disturbance – Short Form – 8a (57), a brief, 8-item instrument assessing sleep disturbance.Fatigue, measured using a 5-item adapted version of the Fatigue Assessment Scale for use in the postpartum population (58) and the Visual Analog of Fatigue Scale (59).Maternal mood, measured with PROMIS Depression – Short Form – 8a and PROMIS Anxiety – Short Form – 8a (60) which measure symptoms of depression and anxiety respectively.Trait and state sleepiness, measured using the Epworth Sleepiness Scale (61) and Karolinska Sleepiness Scale (62) respectively.

#### Other Factors

Demographic, medical conditions, and obstetric information are collected using self-report at baseline (T1) and changes are monitored at T3 and T4 (e.g., infant-feeding method, medical conditions of mother/infant, engagement in therapy, medication use).Postnatal Sleep Questions include self-reported maternal sleep behaviours over the past week (e.g., sleep duration, onset latency, wake after sleep onset, daytime naps adapted from the Consensus Sleep Diary (63).Self-reported maternal sleep history (i.e., pre-pregnancy sleep) are assessed using adapted versions of the PROMIS-SD-SF and Postnatal Sleep Questions.Maternal mental health, measured with the Cross-Cutting Symptoms Level 1 (64).Mother-infant attachment quality, assessed using the Mother to Infant Bonding Scale (65).Relationship satisfaction with the partner, measured using the brief Dyadic Adjustment Scale – 4 (66).The following are assessed and examined as potential covariates: infant sleep [Brief Infant Sleep Questionnaire; (67)]; perceived stress [Perceived Stress Scale; (68)]; social support measured using the PROMIS Instrumental Support – Short Form – 4a and PROMIS Emotional Support – Short Form – 4a (69); questions on the partner's sleep behaviour and overnight assistance with infant care are also included.Feasibility and acceptability are assessed implicitly via recruitment and dropout rates, and explicitly via the Client Satisfaction Questionnaire (70) and qualitative feedback from participants.Due to ongoing data collection during the COVID-19 pandemic, questions related to personal experiences with COVID-19 and potential impact on participation are asked to all participants who completed the project after mid-February 2020 (shortly before the outbreak was declared a national pandemic in Australia). This is intended to assist with interpreting findings from this trial following completion.

The following constructs will also be measured and explored as predictors or mediators of treatment responses:
Vulnerability to insomnia under stress, using the Ford Insomnia Response to Stress Test (71).Maternal self-efficacy, assessed using the Maternal Efficacy Questionnaire (72).Beliefs and attitudes about sleep, using the Dysfunctional Beliefs and Attitudes about Sleep Scale (73).Chronotype via the Morningness Eveningness Questionnaire (74).Sleep effort, using the Glasgow Sleep Effort Scale (75).Participants' perceived credibility and expectancy of treatment via the Credibility Expectancy Questionnaire (76).Intervention adherence (assessing frequency and usefulness of each intervention component).

